### Intervention

The three intervention arms of the RCT consist of HC, HW, and their combination. All participants will receive their risk assessment profile at the beginning of the interventions. In the first arm, participants will receive both HC and HW as interventions. In the second arm, participants will receive only HC, and in the third arm, only HW. Participants in waitlist control will not receive any interventions during the 6-month study period following randomization.

After completion of all follow-up components, participants in the HC-only and waitlist control arm will be rewarded with the HW, while those in the HC + HW arm and the HW-only arm can keep their HW. Additionally, participants in the HW-only and control arm will receive HC after the 6-month assessment. This approach is intended to serve as an incentive to promote compliance and reduce dropout rates.

#### Health coaching (HC)

All health coaches have at least a bachelor’s degree in health, social science, psychology, or science. They were trained by an expert team, that includes a medical doctor, a certified health coach and psychologist, and a certified health and wellness coach trainer from the American Fitness Professionals and Associates (AFPA). The training program includes an 88-h HC training course and individual and group supervisions. Coaches acquire knowledge about HC fundamentals, health behavior, and behavior change techniques based on CBT, MI, and the transtheoretical model. Additionally, ongoing supervision and troubleshooting support are provided by the expert team during program implementation.

HC comprises the following psychometric components: goal-oriented, client-centered, partnership, health-focused, process, enlightening, and empowering [33]. The delivery mode, intervention components, duration, and frequency of follow-up sessions may vary [16, 34]. In general, each coaching session contains the following elements:Discovery (for first sessions) or revision (for follow-up sessions): During initial sessions, coaches explore details regarding participants' lifestyle behavior using the questionnaire results. In follow-up sessions, they review and refine these points.Creating awareness: Coaches help participants recognize their health-related behaviors and patterns.Priorities: Participants and coaches jointly identify key areas for improvement.Planning and goal setting: Based on insights, a tailored action plan is developed collaboratively.

Participants in the HC arm will receive different coaching intensity depending on their NCD risk level (please refer to Table 2 for the definition of NCD risk level). Low-risk and high-risk participants will receive 6 to 10 sessions (co-decided by the participant and the coach), and ≥ 12 sessions during the 6-month intervention period, respectively. In the first coaching session, health coaches will review the participants’ risk profiles and use a 10-point Likert scale to assess their priority, importance, readiness, and confidence to initiate lifestyle changes (higher scores indicate greater priority, importance, readiness, or confidence). The health coach will then employ various skills, adapting to specific situations, to co-design a personalized action plan with specific goals with the participants. Participants will also receive health education through the CORE program to acquire relevant knowledge to achieve these goals. The CORE program covers three topics: physical activity, diet, and mental health. Participants in the HC arm will be assigned to one of these topics, depending on their lifestyle domain risk and their preferences. Follow-up sessions will be conducted face-to-face, via phone, or through text messaging. The participant’s compliance and progress toward the established goals will be continually reviewed, and the action plan will be adjusted as needed.

**Table 2 Tab2:** NCD risk assessment criteria

Assessment metric	Low risk	High risk	Suspected to have NCDs
Health watch	Yes	Yes	Nil
Health coaching	6–10 sessions	At least 12 sessions	Nil
CORE program	Yes	Yes	Nil
**A component**			
BMI^a^	23–24.9 kg/m^2^	≥ 25 kg/m^2^	–
Diet^a,b^	≤ 3 components	≤ 1 component	–
Physical activity^a^	1–149 min/week moderate level of exercise	None—sedentary	–
Smoking^a^	Former smoker, but quit within 12 months	Current smoker	–
TC^a^	TC ≤ 6.2 mmol/L	6.2 mmol/L < TC < 8 mmol/L	–
Family history of HT/DM/CVD in 1 st degree relative < 60 years of age	Yes	Yes	–
Alcohol use	5 ≤ AUDIT-C score < 8	AUDIT-C score ≥ 8	–
**B component**			
BP^a,c^	SBP 120–129 mmHg or DBP < 80 mmHg	SBP 130–134 mmHg or DBP 80–84 mmHg	SBP ≥ 135 or DBP ≥ 85 mmHg
FBG^a^	< 5.6 mmol/L	5.6–6.9 mmol/L	≥ 7 mmol/L
Blood lipids	–	–	TC ≥ 8 mmol/l or TG ≥ 5 mmol/l or LDL ≥ 5 mmol/l
CVD risk	–	–	QRISK3-2018 ≥ 15%
Definition	Not meeting “high-risk” criteria	At least 2 A components and 1 B component above	At least 1 B component above

^a^AHA simple 7 criteria risk factors [91]

^b^The five diet components are as follows: (1) 4.5 cups per day of fruits/vegetables, (2) servings of fish per week (3.5-oz servings), (3) 1500 mg/day of sodium, (4) 450 kcal (36 oz) per week of sweets/sugar-sweetened beverages, and (5) 3 servings per day of whole grains (1.1 g of fiber in 10 g of carbohydrate; 1-oz equivalent servings) [91]

^c^AOBP measurement [47]: Take mean BP readings with 1 min interval between readings. Use the average of this 3 readings. Measurement conditions: 1) Quiet room with comfortable temperature; 2) No smoking, caffeine, food, or exercise for 30 min before measurement; 3) Remain seated and relaxed for 3-5 min; 4) No talking by patient or staff during or between measurements. Measurement posture: 1) Sitting with back supported by chair; 2) Legs uncrossed, feet flat on floor; 3) Bare arm testing on table; mid-arm at heart level

#### Health watch (HW)

Participants assigned to the HW group will receive a Huawei Watch Fit 2 smartwatch (Huawei Technologies Co., Ltd., China). The device tracks various health metrics, including physical activity, daily step counts, and heart rate (HR), serving as an objective tool to assess participants’ overall health status. Participants are encouraged to wear the HW daily. The Huawei Watch Fit 2 underwent internal validation by an optoelectronics expert. The accuracy of SpO2 and HR measurements from Huawei Watch Fit 2 were comparable to those from the COMEN-C502 (Shenzhen Comen Medical Instruments Co., Ltd., China) and the BCI-Autocorr PLUS Digital Pulse Oximeter (Smiths Medical Inc., USA) showing a mean absolute error difference of 2 BPM for HR and 2.2% for SpO2. The HUAWEI Health application, which accompanies the smartwatch, includes built-in workout programs and allows users to set physical activity targets. Participants are required to synchronize their HW with the project cloud. Reminders will be sent to participants who fail to synchronize or without HW data. Technical staff are available via text messaging to assist with any technical issues related to the HW.

#### Health coaching and Health watch (HC + HW)

Participants in the HC + HW group will receive 6 months of HC follow-up along with a Huawei Watch Fit 2 smartwatch. In each follow-up session, health coaches will also utilize data captured by the HW to enrich the HC context.

#### Waitlist control

Participants in the waitlist control group will not receive any of the abovementioned interventions during the 6-month follow-up period.

### Sample size calculation

We used a web-based multi-arm clinical trial sample size calculator [35] for the sample size (or power) calculation. In this four-arm trial, with three experimental treatments and a waitlist arm, the hypotheses to be tested will be:$${H}_{k}:{\tau }_{k}={\mu }_{k}-{\mu }_{0}\le 0,\hspace{0.25em}k=1,\dots ,3.$$

The *global null hypothesis*, $${H}_{G}$$, will be:$${\tau }_{1}={\tau }_{2}={\tau }_{3}=0.$$

The *global alternative hypothesis*, $${H}_{A}$$, will be:$${\tau }_{1}={\tau }_{2}={\tau }_{3}={\delta }_{1}.$$

The *least favorable configuration* for experimental arm $$k$$, $$LF{C}_{k}$$, will be:$${\tau }_{k}={\delta }_{1},\hspace{0.25em}{\tau }_{1}=\cdots ={\tau }_{k-1}={\tau }_{k+1}=\cdots ={\tau }_{K}={\delta }_{0}.$$

Here, *δ*_1_ represents the interesting treatment effect, which was defined as LS7-score difference of 0.44 with a common standard deviation (SD) of 1.57, and *δ*_0_ represents uninteresting treatment effects, which was defined as the smallest mean difference between the intervention and control arm that would make the intervention clinically significant, and was set to be 0 [35]. Due to a lack of evidence, we will not explicitly test the interaction effect of HC and HW. The combined intervention will be analyzed as a distinct arm compared to the control, rather than a factorial combination. Under the global alternative hypothesis, a sample size of (*N* = 720) will have a disjunctive power (power to reject at least one null hypothesis) of 0.901 after Bonferroni’s correction. This estimation used a balanced target group allocation and a 0.05 significance level. The assumed mean and SD were based on our ongoing cohort study of 1862 participants who received HC + HW interventions. The participants in this cohort study have the same eligibility criteria as those in the proposed trial. According to previous studies, an improved LS7 score of 0.44 is considered a significant health improvement [36–38]. We propose a target sample size of 1000, allowing for a dropout rate of up to 28%. However, the observed dropout rate in the cohort study is much lower (3.8%).

### Randomization and blinding

Eligible participants will be allocated to one of the four arms using permuted block and stratified randomization by sex (male/female), age group (35–50 and 50–59), and six study sites in a 1:1:1:1 ratio (with 250 participants in each arm). The randomization lists will be generated by an independent statistician, employing block sizes that vary between 8 and 16, which will remain undisclosed to the research team. The randomization lists will be kept in a password-encrypted file, accessible only to an impartial researcher from the research team. This researcher will handle the allocation procedure and communicate the results to the project health coaches via an online portal. The online system will display only de-identified eligible participants, identified by project ID, who have completed the baseline assessments. Each morning during the recruitment phase, this researcher will assign eligible participant to intervention arm according to the randomization lists. Project health coaches will be able to identify their allocated participants as indicated in the online portal. Subsequently, the health coach will schedule the participant’s first intervention session and inform them of their assigned intervention arm. Due to the nature of the intervention, neither participants nor project health coaches will be blinded to the allocation. However, the research team and the principal investigator (PI) will remain blinded to group assignments. Statisticians responsible for data analysis will remain blinded to group assignments until the analysis is complete. Participants who experience serious adverse events (SAEs) during the trial will be unblinded to the PI or research team.

### Data collection and management

All data will be collected via the project’s online administrative portal. All assessment survey conducted by participants are implemented with range checks for data entry validation. Health assessment data will be entered by project health coaches. Access to the portal backend is restricted to the PI and the research team. The raw personal data of participants will remain strictly confidential and will only be accessible to designated research staff and health coaches. All personal identifiers (e.g., name, HKID, telephone number, WhatsApp) will be removed from the analytical data and replaced with pseudo-identification numbers to ensure participant anonymity. Physical copies of sensitive documents, if any, will be stored in a double-locked filing cabinet in the research office, with access restricted to authorized personnel only. Electronic data will be stored securely on the servers managed by the Information Technology Services Centre (ITSC) of The Chinese University of Hong Kong (CUHK). These servers are protected by firewalls, password access controls, and are monitored 24 h a day. Data access will be restricted to the principal investigator and delegated research staff. All data transfers will utilize encrypted channels. All data will be retained in accordance with institutional guidelines and will not be shared with unauthorized individuals. Data security and confidentiality protocols will be regularly reviewed and updated as necessary. All blood samples will be used exclusively for biochemical testing and will not be retained after the tests have been completed. All blood samples collected from participants at baseline and at the 6-month assessment will be used solely for biochemical testing by private Hong Kong Laboratory Accreditation Scheme (HOKLAS)-accredited laboratories [39]. Samples will not be stored or retained after testing.

As the trial involves low-risk participants and low-risk interventions, a data and safety monitoring committee is not required. The PI will be responsible for monitoring the progress and implementation of the trial. Additionally, the PI will have regular biweekly meeting with the research team and audits throughout the study to ensure adherence to the trial protocol. No interim analysis will be conducted. The PI and research team will meet with NGO representatives monthly for the first 6 months, then quarterly, to review the progress of the trial.

### Severe adverse events (SAEs)

Although the trial is considered to have a relatively low risk of SAEs, any SAE that occurs will be overseen and reviewed by the project’s clinician. SAE are defined as any undesirable medical occurrence that is fatal, life-threatening, results in hospitalization or prolongation of existing hospitalization, causes persistent or significant disability/incapacity, or results in a congenital anomaly/birth defect [40]. We will collect these SAEs from health coaches and participant self-reports. The clinician will assess each case to determine whether participants should be withdrawn from the trial or temporarily suspended from the intervention. All SAE cases will subsequently be reported to the research ethics committee and will be reported in future publications regarding the trial results. Participants who experiences SAE will not receive any ancillary or post-trial care.

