## Trial design

This parallel, 4-arm RCT is designed as a superiority trial to assess the effectiveness of HC and HW, individually or in combination, in promoting a healthy lifestyle among middle-aged individuals without NCDs over a 6-month period. The participants will be aged 35–59 years, at risk of developing NCDs, but without any doctor-diagnosed NCDs. A total of 1000 eligible participants will be randomized equally into one of the four arms in a 1:1:1:1 ratio (*n* = 250 per group). The four arms are HC + HW, HC-only, HW-only, and control. While participants in the three intervention groups will receive their assigned interventions, the control group will not receive any intervention but will be followed up until the end of the trial. The primary assessment time point will be at 6 months after the intervention has started. The secondary assessment will occur at 3 months, during which participants will complete a shorter version of the survey.

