## Outcomes measurement

Blood tests, BP, anthropometric measurements, and a health assessment questionnaire, will be conducted both at baseline and 6 months after randomization. Additionally, participants will receive a shorter follow-up questionnaire at 3 months.

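### One of the two named SAE sources is the health coach, but coaching during follow-up exists in only two of the four arms, so SAE counts may not be comparable across arms

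*Protocol article*

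**What the plan says.** The section on severe adverse events names two sources: "We will collect these SAEs from health coaches and participant self-reports". The project clinician reviews each event, and all cases go to the ethics committee and into the trial publications.

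Participants are "randomized equally into one of the four arms in a 1:1:1:1 ratio", 250 per arm. On coaching, the Health coaching (HC) section says: "Low-risk and high-risk participants will receive 6 to 10 sessions (co-decided by the participant and the coach), and ≥ 12 sessions during the 6-month intervention". For the combined arm: "Participants in the HC + HW group will receive 6 months of HC follow-up along with a Huawei Watch Fit 2 smartwatch". For the other two arms, the Intervention section says that "participants in the HW-only and control arm will receive HC after the 6-month assessment", and the Waitlist control section says that its participants "will not receive any of the abovementioned interventions during the 6-month follow-up period".

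The scheduled contacts common to all arms are in the Outcomes measurement section: a full assessment at baseline and at 6 months, and in between, "participants will receive a shorter follow-up questionnaire at 3 months". Neither follow-up contact is named as an SAE source.

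The Randomization and blinding section states that participants and coaches know the allocation, and that a participant with an SAE is unblinded to the principal investigator or research team.

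**The concern.** When one arm has frequent contact with someone whose role includes passing on SAEs and another does not, recorded counts can differ although the true rates are the same. Here the frequency of that contact is set by randomization.

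Three things are at stake.

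- **Comparison across arms.** SAEs will be published, and readers of a four-arm trial will compare the arms. If events are under-recorded in HW-only and waitlist, coaching looks less safe than it is.
- **Prompt review.** The clinician can assess only events that reach the clinician. A fatal event cannot be self-reported, and without coaching the next scheduled contact may be up to three months away.
- **Blinding.** Because a recorded SAE unblinds the participant to the principal investigator or research team, unequal recording also means unequal unblinding by arm.

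The article states that no data and safety monitoring committee is required, so it describes no independent body that would notice uneven reporting.

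**Working it through.** The article gives no SAE rate, expected count or capture probability, so there is no figure of its own to reproduce. The check has two parts.

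**1. Scheduled contacts after randomization.** Session counts come from the Health coaching (HC) section and Table 2, and assessments from the Outcomes measurement section. I assume the HC + HW arm follows the same session counts, because its own section gives only the duration.

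| | Coached arms, low risk | Coached arms, high risk | HW-only and waitlist |
|---|---|---|---|
| Coaching sessions | 6 to 10 | at least 12 | 0 |
| 3- and 6-month assessments | 2 | 2 | 2 |
| Total | 8 to 12 | at least 14 | 2 |

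Ratios to the uncoached arms are 8/2 = 4, 12/2 = 6 and at least 14/2 = 7. A coached participant therefore has about 4 to 7 or more times as many scheduled occasions on which an event could come to light. These occasions are not all equal, since follow-up coaching may be face to face, by phone or by text. The coach's message about allocation, and the technical messages to watch users, are left out because neither is a scheduled follow-up contact named for SAEs.

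**2. Effect on counts, under assumed values.** With 250 per arm there are 500 coached and 500 uncoached participants. Let the true 6-month SAE rate p be the same in both.

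Expected recorded SAEs = 500 × p × capture probability. The apparent ratio is capture (coached) / capture (uncoached), and p cancels.

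| Assumed capture, coached vs uncoached | Recorded at p = 1% | Recorded at p = 3% | Apparent ratio |
|---|---|---|---|
| Equal | equal | equal | 1.0 |
| 95% vs 80% | 4.75 vs 4.00 | 14.25 vs 12.00 | 0.95/0.80 = 1.19 |
| 90% vs 60% | 4.5 vs 3.0 | 13.5 vs 9.0 | 0.90/0.60 = 1.5 |

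The shortfall in the uncoached arms together is 0.75 to 2.25 events in the second row and 1.5 to 4.5 in the third. The rates and capture probabilities are all assumptions; the article supports the direction but not the size.

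**The case against.** The case on the other side has real weight.

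- **Self-report is open to every arm.** A reader might infer that self-report is spontaneous, so that uncoached participants report only if they think of it. The article does not say whether self-report is prompted. This point stands.
- **Coach contact is not wholly absent from the uncoached arms.** Coaches tell participants their allocation. They also enter the health assessment data, with no restriction by arm, which suggests some coach involvement at 6 months in all four. A non-fatal admission could then be learned of late in any arm. This rules out saying that only two arms see a coach at all. It does not equalize capture: one retrospective contact is not equivalent to 6 to 12 or more sessions, and no SAE enquiry at that visit is described.
- **No by-arm SAE table is promised.** The article says only that cases will be reported in publications, SAEs are not a listed outcome, and no SAE comparison is described. This stands, and it keeps the point modest.
- **SAE reports are not the only safety information.** Blood pressure, blood tests, anxiety and depression are also measured at baseline and 6 months.
- **The full protocol, not shown, may contain an SAE question.** It may. But the article does not simply leave the method open: it names the sources, and access to one of them depends on the arm.
- **It may be too late.** Recruitment ended on 30 September 2024 and the article appeared on 8 October 2025, so follow-up may be over. At protocol version 4 (15 October 2024), however, almost all final assessments lay ahead, since only 2 participants had completed them by 29 October 2024. The reporting part of the remedy applies whenever the assessments end.

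**Conclusion.** The point holds in a limited form. As described, SAE ascertainment is likely to be more intensive in HC and HC + HW than in HW-only and waitlist, because one of the two named sources comes with scheduled coaching. Under-recording in the uncoached arms is probable, and counts may not be comparable across arms.

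The document does not support a claim that the counts will be biased or that events will be missed. A reader might also infer that recorded SAEs would nearly double with coaching. A ratio of 1.9 does follow from 95% against 50% capture (0.95/0.50), but the 50% is purely assumed. The same arithmetic gives 1.19 at 95% against 80%, and 1.0 if capture is equal.

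The conclusion rests on two assumptions: that more scheduled coach contact leads to more events being heard of, and that no common SAE question is already asked in all arms. Should such a question exist in the full protocol, most of the concern falls away. The trial is described as low risk and few events are likely, but with few events a difference of one to four can change the impression.

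**What to change.** - Ask one identical SAE question, using the article's own SAE definition and recording dates, in all four arms at the 3-month and 6-month assessments. For participants already past 3 months, let the 6-month question cover the whole period.
- Base any between-arm SAE summary on that question.
- Keep the coach route for prompt reporting to the clinician, and report events known only through coaching contacts separately.
- Where assessments are already complete, state the unequal ascertainment when SAEs are published, and still separate the events known only through coaching as far as the records allow.

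The cost is one added questionnaire item and a line or two of reporting. The downside is a slightly longer questionnaire and, for some participants, recall over six months instead of three. The design, randomization and primary analysis are unaffected.
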